Given the opportunities that early childhood presents for intervention to support and enhance parent-child relationships, a number of attachment-based parenting intervention approaches targeting high-risk children and caregivers have been developed [29]. Examples include Video-feedback Intervention to promote Positive Parenting and Sensitive Discipline (VIPP-SD) [30], Attachment and Biobehavioral Catchup (ABC) [31, 32], and the Circle of Security Intensive Intervention (COS-I) [33]. Each of these interventions aims to address parenting sensitivity and some explicitly target infant attachment and disruptive/externalizing child behaviors. Evidence for the efficacy of these programs in relation to the specific age of toddlerhood (12–24 months) and for reducing disruptive child behaviors, however, is limited and equivocal. VIPP-SD [30] involves review of video-taped parent-child interaction sessions in the home and aims to increase parental sensitivity and sensitive parental discipline, defined as the ability to take into account the child’s perspective and signals when discipline is required. VIPP-SD has been shown to be effective in enhancing maternal attitudes toward sensitivity and sensitive discipline and in promoting sensitive discipline interactions. The intervention also resulted in decreased overactive problem behaviors, but only among children in families with elevated levels of marital discord and daily hassles (e.g., money problems or troubles at work); child externalizing behaviors remained unchanged. ABC is based around active coaching of the parent from a therapist in ten 1-h home-based sessions, with coaching focused specifically on enhancing nurturance of the child, following the child’s lead with delight, and reducing frightening/intrusive behavior. ABC has been shown to be associated with a range of positive outcomes including decreased rates of disorganized attachment and increased rates of secure attachment [34], normalized diurnal cortisol production in children [35], enhanced child executive functioning [36], and improved emotion expression [37]. The efficacy of the program for disruptive or externalizing behavior in the toddler age group, however, has not been specifically demonstrated. COS-I comprises a mix of individual and group components spread over 20 weeks, and aims to increase caregiver sensitivity and responsiveness to child cues, empathy for the child by supporting parental reflective functioning, recognition and understanding of child attachment cues, and awareness of the impact of the caregiver’s own attachment history on caregiving. COS-I has not yet been evaluated using a RCT but open trial designs suggest positive changes in terms of child attachment security, internalizing and externalizing symptoms, and in parenting stress and parent mood problems [38–41]. Given the wide age range in these studies (1–8 years), specific outcomes for toddlers aged less than 2 years are unknown. Taken together, it is clear that there is a need for new intervention models to address the unique needs of parents and toddlers in the 12–24 age range experiencing early onset disruptive or externalizing behaviors.

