We thus hypothesize that from baseline (‘Time 1’) to post-treatment/waitlist (‘Time 2’) there will be a gradient effect, whereby parent-child dyads who receive PCIT-T will show the greatest gains and parent-child dyads who receive no treatment will show the least gains with respect to the following variables:
Improved parenting capacity through increased i) labeled praise of the child, ii) parenting sensitivity, iii) parent sense of competence in managing negative toddler emotions, iv) parent mentalizing about the child, and v) parent emotion regulation; and decreased i) negative statements directed toward the child, ii) parent sense of caregiving helplessness, iii) child abuse potential, and iv) parental stress.Improved child outcomes including increased: i) emotion regulation maturity; ii) social-emotional functioning including initiative, relationship functioning and self-regulation, iii) attachment security, and iv) decreased externalizing behavior.

Second, we expect that for the two active treatment conditions, this gradient effect will be maintained at a 4-month post-treatment follow-up, whereby parent-child dyads that receive PCIT-T will show superior outcomes on all variables compared to parent-child dyads where the parent received COS-P.

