*Positive and negative parenting* during the 20-min parent-child interaction will be coded according to the Dyadic Parent-Child Interaction Coding System, Fourth Edition, a coding scheme designed to rate parent-child verbal interactions and responses during observed interactions [52]. The DPCIS has been shown to have high levels of reliability, with kappa coefficient scores typically over .80 [53, 54]. Trained DPICS coders will view the video-recorded parent-child interaction sessions, create a moment-by-moment transcript of the parent-child interactions, and use the transcription and video to code every parent verbalization. A ‘positive parenting’ score (total number of labeled praises) and a ‘negative parenting’ score (total number of negative statements) will be calculated based on the number of times these verbalisations are observed during the five structured situations. To create standardized scores, frequency counts will be transformed into ratios based on the following: 1) total number of labelled praises divided by total number of verbalisations, and 2) total number of negative statements divided by total number of verbalizations.

*Parenting sensitivity* during each episode of the 20-min parent-child interaction will be coded using the NICHD Study of Early Child Care and Youth Development: Sensitivity Scales (NICHD-SECCYD) [55]. This coding system has demonstrated reliability (intra-class coefficents typically .8 and over [56, 57]) and validity (positive associations with infant attachment quality [56–58], and sensitivity to change following parenting interventions [59]). The NICHD-SECCYD sensitivity scales yields a composite parental sensitivity score, calculated by summing scores on six scales, each scored on a 4-point scale whereby higher scores indicate that the variable is more characteristic of the parent: sensitivity, positive and negative (reversed) regard for the child, intrusiveness, respect for autonomy and hostility (reversed).

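### The parenting sensitivity composite reverses negative regard and hostility but adds intrusiveness unreversed, so lower intrusiveness lowers the sensitivity score

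*Protocol article*

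**What the plan says.** The parenting sensitivity paragraph of the Measures section says that the coding system "yields a composite parental sensitivity score, calculated by summing scores on six scales". Each of these is "each scored on a 4-point scale whereby higher scores indicate that the variable is more characteristic of the parent". The six components are then listed as "sensitivity, positive and negative (reversed) regard for the child, intrusiveness, respect for autonomy and hostility (reversed"). The reversal mark stands on negative regard and on hostility. It does not stand on intrusiveness, and nothing elsewhere in the article supplies it.

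The hypotheses (Study aims and hypotheses) fix the direction of benefit: "Improved parenting capacity through increased i) labeled praise of the child, ii) parenting sensitivity". Table 1 lists the measure at T1, T2 and T3. The opening of the Measures section states that coders of observational measures are masked to condition and time point.

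**The concern.** Because a higher raw score means more of the named feature, a high intrusiveness score describes a more intrusive parent. Added unreversed, it counts towards sensitivity and pulls against respect for autonomy, its natural counterpart in the same sum. The article itself regards intrusiveness as undesirable: in the Background, one of the coaching aims of a related attachment-based programme is "reducing frightening/intrusive behavior".

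Parenting sensitivity is a hypothesised outcome and one of the few rated by masked coders. The questionnaires, by contrast, are completed by parents who know which treatment they received. A component with the wrong sign weakens any real effect on this outcome, and could reverse it if an arm changed intrusiveness more than the rest of the composite. Double-coding 25% of cases would not reveal the problem, because it arises when the ratings are summed and not when they are made.

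**Working it through.** The article gives no score range, SD, correlation or power figure for this composite, so there is no stated figure to reproduce. The check has two parts: the direction of the score, which follows from the text, and the size of the loss, which needs assumptions.

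**1. Direction of the score**

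Inputs from the Measures section: six scales, unweighted sum, four points per scale, higher meaning more of the feature, and negative regard and hostility reversed. The anchors are not stated. I take 1 to 4; 0 to 3 gives the same differences.

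- As written: sensitivity + positive regard + (5 − negative regard) + intrusiveness + autonomy + (5 − hostility)
- With intrusiveness reversed: the same sum with (5 − intrusiveness)

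Hold sensitivity, positive regard and autonomy at 3, and negative regard and hostility at 2. The other five components then contribute 3 + 3 + 3 + 3 + 3 = 15.

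| Intrusiveness | As written | Reversed |
|---|---|---|
| 4 | 19 | 16 |
| 3 | 18 | 17 |
| 2 | 17 | 18 |
| 1 | 16 | 19 |

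With the other five scales at their best (4 × 5 = 20), the most intrusive parent scores 24 of 24 as written and the least intrusive scores 21. Reversal swaps these. Over the full range of intrusiveness the change is −3 as written and +3 when reversed, a discrepancy of 6 points on a composite that spans 18 (6 to 24).

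**2. Size of the loss**

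Assumptions, none of them in the article: equal SDs, the same favourable shift on every scale, and a common correlation r between scales once all point the same way.

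- Correct sum: signal 6 units, variance 6 + 30r.
- As written, five signs positive and one negative: signal 5 − 1 = 4 units. Of the 15 pairs, 10 add and 5 subtract, so the variance is 6 + 2(10 − 5)r = 6 + 10r.
- Ratio of standardised effects: [4/√(6 + 10r)] ÷ [6/√(6 + 30r)].
- The sample-size equivalent is the square of that ratio.
- Correlation of the two sums: (4 + 20r)/√[(6 + 30r)(6 + 10r)], which simplifies to the same value as the effect ratio.

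| r | As written | Correct | Effect kept (= correlation) | Squared | Sample-equivalent loss |
|---|---|---|---|---|---|
| .1 | 4/√7 = 1.512 | 6/√9 = 2.000 | .756 | .571 | 43% |
| .3 | 4/√9 = 1.333 | 6/√15 = 1.549 | .861 | .741 | 26% |
| .5 | 4/√11 = 1.206 | 6/√21 = 1.309 | .921 | .848 | 15% |

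On the effect-size scale, a 0.5 SD favourable shift on every component with r = .2, .4 or .6 gives d = 0.87, 0.71 or 0.61 for the correct sum, and 0.71, 0.63 or 0.58 as written.

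**3. When the sign would flip**

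The as-written change equals the net favourable change on the other five scales minus the fall in intrusiveness. It turns negative only when the fall in intrusiveness exceeds that net change. If autonomy rises by exactly as much as intrusiveness falls and nothing else moves, the as-written score does not change at all, whereas the correct score rises by twice that amount.

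**The case against.** The strongest reply is that this is a missing word and not a scoring error. The article applies a named, published coding system and condenses its composite into one sentence. Two adverse scales are reversed, so the intended direction is plain. Neither the scoring code nor the coding manual is available, so it cannot be shown that the outcome will be computed wrongly. That stands as far as it goes: a dropped word is the likeliest cause. It does not make the sentence correct. The article marks reversals scale by scale and states the raw direction, so anyone who scores from it will give intrusiveness the wrong sign.

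Three further points limit the consequence, and they also stand.

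- A parent who becomes less intrusive has a lower total only if the other scales do not improve enough to offset it. Dilution is the ordinary result.
- Neither PCIT-T nor COS-P is described as acting mainly on intrusiveness, and the Background remark about reducing it concerns a programme not tested here. Reversal of the effect is therefore a possibility and not a prediction. PCIT-T does teach parents to cut back on commands, questions and criticism, which may lower rated intrusiveness, but the article does not say so.
- The percentages depend on assumed correlations. The 43% figure needs r = .1, which is low for scales meant to form one construct. At r = .3 to .5 the effect kept is 86 to 92%.

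Parenting sensitivity is also one of nine parenting outcomes in Table 1, and the raw scale scores would allow the composite to be re-summed later without new data.

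**Conclusion.** The concern holds. As stated in Measures, the composite gives one of its six components the wrong sign. That much rests on the text alone and needs no assumption beyond a plain reading of "higher scores indicate that the variable is more characteristic of the parent".

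The size is conditional. Under equal SDs and equal response, 76 to 92% of the standardised effect remains for r from .1 to .5, and the as-written score correlates .76 to .92 with the correct one. Reversal of a treatment effect would require a change in intrusiveness larger than the net change on the other five scales.

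The damage is confined to parenting sensitivity at T1, T2 and T3. The sample size rests on the CBCL externalizing score, and randomization, masking and the other outcomes are untouched. Whether the actual scoring is wrong, or only its description, cannot be settled from the article. The correction should be made before the composite is computed, because it is a defined outcome and costs almost nothing to put right.

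**What to change.** - In Measures, write 'intrusiveness (reversed)' in the list of components, and confirm that the scoring code subtracts intrusiveness in the same way as negative regard and hostility. If the scale is in fact coded as non-intrusiveness, correct its label instead.
- Before any group comparison, check on T1 data pooled across arms that each scored component correlates positively with the sum of the other five. Leave the component itself out of the total. Under the assumptions above, a mis-signed component has covariance 1 − 5r with a total that includes it, which is still positive when r is below .2. Its covariance with the other five is −5r, which is negative for any positive r.

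The cost is one word in the protocol, one line of scoring code and one table of correlations. No new data or recoding of video is needed.

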### Statistical analysis

Continuous outcome variables will be analyzed across three time conditions (T1, T2, T3) using a linear mixed models repeated measures design. For all continuous variables, group differences will be tested with family-wise adjustments made to the raw *p*-values to account for multiple comparisons using Holm’s [80] stepdown Bonferroni procedure. Group by time interactions will be examined in fixed effects models, with planned comparisons constructed to examine the differences between the three groups at T2, and between the PCIT-T and COS-P groups at T3. Intention-to-treat analyses (ITT) [81] will be used, with participants included in the analyses within their randomly assigned treatment condition regardless of the amount of treatment received and group mean values estimated based on all observed data of those in the ITT sample. The clinical significance of differences on continuous study variables (from T1 to T2) will be assessed using Cohen’s *d* with effect sizes evaluated using Cohen’s [82] guidelines. Reliable change index scores will also be calculated to assess whether the magnitude of individual-level change on continuous study measures exceeds the margin of measurement error [83]. To examine changes in categorical SSP classifications from T1 to T3 (SSP not administered at T2), generalized linear mixed models with binomial distribution and logit link will be conducted with insecure attachment (0/1) and disorganized attachment (0/1) as dependent variables.

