### Sample size and power calculations

Required sample size was calculated to detect a group by time interaction of moderate size (*f* = .21), for 3 groups and 2 time points (T1 and T2). The effect size *f* is defined as *f* = *σ*_*m*_*/σ*, where *σ*_*m*_ is the standard deviation (*SD*) of the effect of interest and *σ* is the common error *SD*. Cohen (1963) suggested that *f* of .25 is a moderate effect. This effect size was chosen because (a) it is a reasonable and achievable statistical effect, and (b) it is substantively and clinically meaningful for the primary outcome measures. The CBCL externalizing subscale score was used in the power calculation because of all the measures in the study (a) it is the one that corresponds most directly to the presenting problem for most participants; and (b) it was used in a previous study conducted at the same site and with a similar study sample, allowing us to obtain realistic estimates of mean CBCL externalizing subscale scores for T1, and for the PCIT-T group at T2. Based on our previous research using a similar sample and the CBCL externalizing subscale as an outcome measure [48], at T1, all groups were assumed to have a mean of 24. Means at T2 were assumed to be 13 (PCIT-T), 16 (COS-P) and 22 (Waitlist). A common SD of 9 and a correlation between measurements of .6 were specified and it was calculated that assuming alpha of .05 and 80% power, a minimum total of 48 participants (i.e. *n* = 16 in each group) would be required. Post hoc testing of differences between the three groups at T2, and a PCIT-T versus COS-P difference at T3, show that *n* = 30 in each group would give 80% power to detect a mean difference between groups of at least 8.0, with *SD* of 9. And alpha of .05/4, to correct for multiple comparisons for all group comparisons at T2 (PCIT-T versus COS-P, PCIT-T versus Waitlist, COS-P versus Waitlist) and T3 (PCIT-T versus COS-P).

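### Holm is valid for the four planned contrasts but ignores the link among the three at T2; a logically restricted step-down controls the same error and gains about 3 to 7 points of power for COS-P versus waitlist

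*Protocol article*

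**What the plan says.** The Statistical analysis section of the protocol article applies a family-wise adjustment to the group differences on every continuous outcome, "to account for multiple comparisons using Holm’s [80] stepdown Bonferroni procedure". The same section names the contrasts: "planned comparisons constructed to examine the differences between the three groups at T2, and between the PCIT-T and COS-P groups at T3". That makes three pairwise contrasts at T2 and one at T3.

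The Sample size and power calculations section confirms the count. It powers the pairwise contrasts with "And alpha of .05/4, to correct for multiple comparisons for all group comparisons at T2" and the one at T3. On that basis it states that 30 per group "would give 80% power to detect a mean difference between groups of at least 8.0" with an SD of 9. Neither section makes use of any logical relation among the contrasts.

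**The concern.** Holm tests the ordered p-values at α/4, α/3, α/2 and α. Those divisors are needed when any combination of true and false nulls is possible. Here it is not. Write the T2 means as P (PCIT-T), C (COS-P) and W (waitlist). If P = W is false, then P = C and C = W cannot both be true. So after one T2 rejection at most two nulls can still be true, one at T2 and the one at T3, and dividing by 2 is enough where Holm divides by 3. After one T2 rejection and the T3 rejection at most one null can be true, so full α is enough where Holm uses α/2.

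PCIT-T versus waitlist has the largest assumed difference and is usually rejected first. The contrasts that follow it, above all COS-P versus waitlist, are then tested more strictly than error control requires. The rule covers all continuous outcomes, so the loss recurs on each.

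**Working it through.** **Inputs from the article (CBCL externalizing).** At T1 "all groups were assumed to have a mean of 24". For T2, "Means at T2 were assumed to be 13 (PCIT-T), 16 (COS-P) and 22 (Waitlist"). The SD is taken as 9 throughout and the correlation between time points as .6. There are 30 per group and four contrasts. The T2 differences are 22 − 13 = 9 (PCIT-T vs waitlist), 22 − 16 = 6 (COS-P vs waitlist) and 16 − 13 = 3 (PCIT-T vs COS-P).

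**Assumptions.** Tests are two-sided (not stated). No T3 mean is given. The base case keeps the 3-point T2 gap at T3, and 0 to 6 is shown as a range.

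**The article's own figures reproduce.**
- Pairwise power: a two-sample t-test with n = 30 per group, difference 8.0, SD 9 and α = .05/4 = .0125 gives 80.3% on 58 df and 81.1% on 87 df (stated: 80%).
- Interaction effect: the T1–T2 changes are −11, −8 and −2, with mean −7. Halved deviations are −2, −0.5 and 2.5. So σ_m = √[(4 + 0.25 + 6.25)/3] = √3.5 = 1.87, and f = 1.87/9 = 0.208 (stated: .21).

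**Divisors.**

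| Rejected so far | Holm | Restricted step-down |
|---|---|---|
| none | 4 | 4 |
| one T2 | 3 | 2 |
| T3 only | 3 | 3 |
| two T2 | 2 | 2 |
| one T2 and T3 | 2 | 1 |
| any three | 1 | 1 |

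No entry exceeds Holm's, so the restricted procedure cannot reject less.

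**Analytic check of the step that matters.** For COS-P vs waitlist, SE = 9√(2/30) = 2.324 and 6/2.324 = 2.582. Power is Φ(2.582 − z).
- α/3 = .0167: z = 2.394, power 57.5%.
- α/2 = .025: z = 2.241, power 63.3%.

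That is a gain of 5.9 points before rounding, if PCIT-T vs waitlist has already been rejected and T3 has not. PCIT-T vs waitlist has about 91% power.

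**Simulation of the full procedures.** Each scenario used 200,000 to 400,000 trials, with t-tests and both procedures applied to the same four p-values. Three error SDs were used:
- raw: 9
- change score: 9√[2(1 − .6)] = 8.05
- baseline-adjusted: 9√(1 − .6²) = 7.2

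Power for COS-P vs waitlist, Holm → restricted:

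| T3 difference | Raw SD 9 | Change, SD 8.05 | Adjusted, SD 7.2 |
|---|---|---|---|
| 0 | 56.3% → 61.2% | 68.2% → 72.5% | 79.6% → 82.6% |
| 3 | 57.5% → 63.0% | 69.9% → 74.6% | 81.4% → 84.6% |
| 6 | 60.9% → 67.9% | 73.3% → 79.1% | 84.5% → 88.2% |

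Repeat runs differ by about 0.1 point. The gain at a T3 difference of 3 is about 5.5, 4.8 and 3.3 points.

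**Other results.**
- PCIT-T vs COS-P at T2 gains about 2 to 4 points (raw SD, T3 difference 3: 15.9% → 18.8%). PCIT-T vs waitlist and the T3 contrast gain about 2 points or less.
- All three T2 contrasts rejected, T3 difference 3: 7.2% → 7.7% (raw), 12.7% → 13.3% (change), 20.6% → 21.2% (adjusted). Across the scenarios the gain is about 0.2 to 1 point.
- Family-wise error: 4.3% for both procedures under the complete null; 4.1% (Holm) and 4.5% (restricted) under a partial null. No run exceeded 4.6%.
- Trials in which Holm rejected a contrast and the restricted procedure did not: none.

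**The case against.** The strongest reply is that Holm is a standard, transparent and valid choice, fixed in advance, and that the pairwise power statement at .05/4 matches its first step. That stands. A reader might infer that the plan contains an error or fails to control type I error; the documents do not support that. The point is lost efficiency only.

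A second reply concerns size. A reader might quote a loss of about 6 points. That is close to the result on the raw SD of 9, which the article does use for its pairwise power. The planned analysis, however, is a repeated-measures mixed model with group-by-time interactions, and change scores or baseline adjustment come closer to it. The gain is then smaller, and with baseline adjustment Holm already gives about 80% or more on this contrast.

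A third reply concerns importance. The Study aims and hypotheses section predicts a gradient across the three arms, and a reader might infer that the choice of procedure decides whether it can be shown. It does not: the chance of rejecting all three T2 contrasts hardly moves. The bottleneck is the assumed 3-point PCIT-T versus COS-P difference, against the 8.0 that the trial can detect with 80% power. COS-P versus waitlist, the contrast that gains most, does not itself evaluate PCIT-T, the subject of both study aims.

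Finally, part of the extra power comes from using more of the 5% allowance (4.1% to 4.5% in the partial-null run). That is legitimate, since the limit is still respected, but it is not a zero change in actual error.

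**Conclusion.** The point holds as a minor, free improvement. For the four contrasts within one outcome, a step-down with the same family-wise 5% guarantee, needing no assumption beyond Holm's, is uniformly at least as powerful. The benefit falls mainly on COS-P versus waitlist: about 3 to 7 points, depending on how baseline enters the model and on the T3 difference, which the article does not give. PCIT-T versus COS-P at T2 gains 2 to 4 points.

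The figures rest on the article's CBCL means, SD and correlation, on 30 analysed per arm, on two-sided tests, and on reading the family as four contrasts per outcome. The sample size section implies that family; the analysis section does not define it in words. Even with the change, COS-P versus waitlist reaches only about 63% on the raw SD with a T3 difference of 3, because its assumed difference of 6 lies below the 8.0 the trial is powered for.

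**What to change.** In the Statistical analysis section, replace Holm by Shaffer's logically restricted step-down, equivalently closed testing with Bonferroni local tests. State that the family is the three pairwise T2 contrasts plus PCIT-T versus COS-P at T3, within each outcome. Order the p-values and test the next smallest at:
- α/4 at the first step;
- α/2 after any T2 rejection while T3 is not rejected;
- α/3 if only T3 has been rejected;
- α once T3 and at least one T2 contrast have been rejected, or once all three T2 contrasts have been rejected.

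Stop at the first non-rejection. The text must name the version that conditions on which hypotheses were rejected. The version that only counts rejections has divisors 4, 3, 2, 1 here and is identical to Holm.

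The cost is a sentence or two in the analysis section and a few lines of code. The family, the 5% level, the sample size and the data collected stay as they are.

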#### Randomization

Participants who meet the study inclusion criteria will be randomly assigned to receive one of the three conditions using restricted block randomization, using block sizes of *n* = 6. This means that within each block of *n* = 6, 2 participants will be allocated to the PCIT-T condition, 2 participants will be allocated to the COS-P condition and 2 participants will be allocated to the Waitlist condition. The order will be randomized within each block. Figure 1 shows the way that participants will flow through the three assessment points for the study (Time 1, T1; Time 2, T2; Time 3; T3). Randomization will occur at the start of the first face-to-face assessment session (T1), with allocations pulled out of pre-prepared sealed envelopes, but the research team and family will not be informed of the condition to which they have been allocated until after completion of the entire T1 assessment.

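### The planned T2 and T3 group contrasts are worded and powered without baseline adjustment, which gives up precision the T1 data could supply

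*Protocol article*

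**What the plan says.** Under Statistical analysis, the protocol article states: "Continuous outcome variables will be analyzed across three time conditions (T1, T2, T3) using a linear mixed models repeated measures design". On the model terms it says: "Group by time interactions will be examined in fixed effects models". The rest of that sentence defines which contrasts will be tested: "with planned comparisons constructed to examine the differences between the three groups at T2, and between the PCIT-T and COS-P groups at T3". The section mentions neither T1 as a covariate nor a constraint that the arms share one T1 mean.

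Under Sample size and power calculations, the correlation appears once: "A common SD of 9 and a correlation between measurements of .6 were specified". It belongs to the two-time-point calculation for the interaction on CBCL externalizing, which gives a minimum of 48 participants. For the pairwise comparisons the text says that 30 per group "would give 80% power to detect a mean difference between groups of at least 8.0", with SD 9. It adds: "And alpha of .05/4, to correct for multiple comparisons for all group comparisons at T2" and the one comparison at T3. No correlation enters that statement. The assumed values are: "Means at T2 were assumed to be 13 (PCIT-T), 16 (COS-P) and 22 (Waitlist"), from a common T1 mean of 24.

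**The concern.** The hypothesised gradient (PCIT-T best, then COS-P, then waitlist) is answered by the pairwise contrasts, not by the omnibus interaction. Having T1 in the model as an outcome helps the interaction test, and helps when later values are missing. It does not sharpen a difference between groups at T2 if each arm has its own free T1 mean and the data are complete: the estimate is then the raw difference in T2 means.

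Randomisation makes the T1 means equal in expectation, and the plan itself expects T1 to explain a good part of T2. Leaving that unused gives larger standard errors than the same data allow. It also leaves chance T1 imbalance between small arms in the T2 comparison.

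**Working it through.** **Inputs, all from the protocol article.** SD 9, T1-T2 correlation .6, alpha .05/4 = .0125, assumed T2 means 13, 16 and 22 (Sample size and power calculations); 30 per arm, from 90 families allocated equally (Randomization). Assumed here: two-sided tests, complete data, and noncentral t with 58 degrees of freedom.

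**1. Reproduce the plan's figures.**
- Interaction: the assumed changes are -11, -8 and -2, with mean -7. The interaction effects per cell are half the deviations, ±2, ±0.5 and ±2.5. Their root mean square is sqrt(3.5) = 1.871, so f = 1.871/9 = .208 (stated .21). With noncentrality f² × N × 2/(1 - .6), N = 48 gives 80.3% power. The stated 48 reproduces, using the correlation.
- Pairwise: the standard error of a raw difference is 9 × sqrt(2/30) = 2.32. For 8.0 points, power is 80.3%. The stated 80% reproduces, without the correlation.

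**2. Variance of a T2 contrast under three analyses.** Relative to a raw T2 difference (variance 81 × 2/30 = 5.40):
- group-by-time model with free T1 means, difference at T2: factor 1, variance 5.40;
- difference in change from T1: factor 2(1 - .6) = .80, variance 4.32;
- common T1 mean, or T1 as covariate: factor 1 - .6² = .64, variance 3.456, SD 9 × sqrt(.64) = 7.2.

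A generalised least squares calculation for three groups and two times gave the same three factors.

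**3. Consequences with 30 per arm and alpha .0125.**

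| | Raw T2 difference | Change from T1 | Baseline-adjusted |
|---|---|---|---|
| Power for 8.0 points | 80.3% | 89.4% | 95.4% |
| Detectable difference, 80% power | 7.98 | 7.13 | 6.38 |
| Power, PCIT-T v waitlist (22 - 13 = 9) | 90% | 96% | 99% |
| Power, COS-P v waitlist (22 - 16 = 6) | 51% | 62% | 74% |
| Power, PCIT-T v COS-P (16 - 13 = 3) | 11% | 14% | 18% |

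Only the first column matches the stated 80% for 8.0 points.

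**4. Equivalent sample.** Against a raw difference: 1/.64 = 1.56, so 30 per arm acts as 30/.64 = 46.9, about 47. Against a change contrast: .80/.64 = 1.25, or a standard error smaller by 1 - sqrt(.64/.80) = 11%.

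**5. Chance imbalance.** A T1 difference between two arms has standard error 2.32 points. At correlation .6, 0.6 × 2.32 = 1.4 points of a one-standard-error imbalance carries into a raw T2 difference.

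**6. Other correlations.** The document gives none for T3 or for other outcomes. The gain over a raw difference, 1/(1 - rho²), is 1.19 at .4, 1.33 at .5, 1.56 at .6 and 1.96 at .7.

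**The case against.** The strongest reply is that the plan does not ignore T1. T1 is an outcome in the model, group-by-time interactions are tested, the hypotheses speak of gains from T1 to T2, and the effect sizes concern T1-to-T2 differences. On that view the planned comparisons may be contrasts in change, and the cost is 25% in effective sample rather than 56%. With an unstated common-baseline constraint it would be nil. This stands: the text does not settle the contrast, and a reader who inferred that the baseline is discarded altogether would go too far.

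A reader might also infer that the pairwise power is wrong, or that the comparisons are biased. Neither follows. An SD of 9 without correlation is a conservative planning choice, and raw T2 differences between randomised arms are unbiased.

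Contrast coding is often left to an analysis plan, and none is shown here. Silence alone would not be a finding. Here, though, the wording of the comparisons and the pairwise power calculation both point to unadjusted differences.

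The size is also limited in scope. The .6 is given for CBCL externalizing between T1 and T2 only. The fixed alpha of .0125 is stricter than the Holm procedure the plan names, so power under Holm would be somewhat higher in every column.

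Finally, adjustment needs a T1 value obtained before treatment. The Time 1 assessment section has the questionnaires completed at home and handed back at the T2 session. If that is literal, adjusting for T1 CBCL could introduce bias that a raw T2 difference avoids. This stands as a condition on the fix.

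**Conclusion.** The point holds as a loss of precision in the planned contrasts. As worded and as powered, they are unadjusted group differences, and having T1 in the model does not sharpen them when data are complete. For CBCL externalizing at T2, with correlation .6 and complete data, adjustment would leave 64% of the variance of a raw difference, or 80% of the variance of a change contrast if that was meant. The practical effect is greatest for COS-P against waitlist. The 3-point PCIT-T against COS-P difference stays poorly powered at 18% even with adjustment. For T3 and the other continuous outcomes, the size depends on correlations that the document does not give.

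**What to change.** State under Statistical analysis that the planned T2 and T3 contrasts come from either a constrained longitudinal model (one common T1 mean across arms, group effects only at T2 and T3) or a model with T1 as covariate. The constrained model has the advantage of keeping children without a T1 value. This matters for DECA self-regulation, because the infant version completed by younger children lacks that scale.

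The pairwise power with SD 9 may stay as a conservative figure. Beside it, give the adjusted one (SD 7.2, detectable difference 6.4), marked as conditional on a correlation of .6.

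Before either change, reconcile the Time 1 assessment wording on the return of T1 questionnaires, so that T1 measures are clearly completed before treatment. The cost is a few sentences, with no new data, no extra visits and no change to the sample size.
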